### Data management and analysis

2.7

The data will be double-checked and entered into an Excel file with password protection for centralized management and stored on a dedicated research computer. During the data entry process, information will be de-identified and encrypted to protect the privacy of the participants. Only authorized personnel from our research team can access the data for analysis. An independent researcher not involved in the study implementation will be responsible for the regular monitoring of the data collection procedure.

#### Quantitative data analyses

2.7.1

Quantitative data analyses will be conducted using IBM SPSS Statistics for Windows (Version 26.0. Armonk, NY: IBM Corp), with all statistical tests being two-sided and significance set at 0.05. The outcomes will be analyzed with an intention-to-treat approach (63). As for statistical description, the count data, such as gender will be presented as “frequency” and “percentage.” The continuous data that conform to the normal distribution (assessed by the W test coupled with a histogram) will be described using means ± standard deviation. As for group differences at baseline, post-intervention, and follow-up, *t-test* or Mann–Whitney *U* test will be performed for continuous variables; Pearson χ2 tests or Fisher exact test will be used for dichotomous variables. The generalized estimating equation (GEE) model, which could test the effects of group, time, and their interactions, will be used to analyze the effects of the intervention. Covariance (if any found in the baseline comparison) will be adjusted during the analysis of intervention effects. Cohen’s *d* will be used as the unit measure of effect size, and is interpreted as follows: 0.2 represents a small effect, 0.5 a moderate effect, and 0.8 a large effect. Cohen’s *d,* calculated by using the formula “difference in treatment and control group means divided by the pooled standard deviation,” is applicable for small sample sizes (64).

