### Sample size and sampling

2.6

The central limit theorem posits that a minimal sample size of 30–40 is enough for determining the mean, standard deviations, and 95% confidence intervals (58). This pilot RCT aims to assess the feasibility, acceptability, and preliminary effectiveness of the AOMI intervention, utilizing a generally acceptable sample size for preliminary analysis to evaluate intervention feasibility and estimate the between-group effect. Specifically, each study group will have 18 individuals to identify a standardized effect size of 0.40 with 80% power and a two-sided significance level of 5% (59). Taking into account a potential attrition rate of 20%, 23 participants per group (i.e., 46 participants in total) will be recruited by using convenience sampling. For one-on-one interviews, we will use a purposeful sampling of key informants, including those who completed at least 60% of the intervention sessions and those who did not, until we reach information saturation and find no relevant new codes in the data (60).

For MRI scans, a liberal threshold of *α* = 0.05 requires 24 participants (12 per group) to achieve 80% power at the single-voxel level for typical activations (61). To control error rates in multiple comparisons, doubling the number of participants is recommended to maintain this level of power. Due to the challenges of MRI data collection, each group will consist of a minimum of 12 participants undergoing pre- and post-intervention MRI scans. Notably, this sample size aligns with the median sample size observed in highly cited clinical fMRI studies published over the last three decades (62).

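### GEE is the test of the intervention effect with only 36 to 46 participants; if the ordinary uncorrected robust Wald test is used, the 5% group-by-time test runs at about 7 to 8%

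*Protocol article*

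**What the plan says.** Under Quantitative data analyses the protocol article fixes the software ("Quantitative data analyses will be conducted using IBM SPSS Statistics for Windows"), the threshold ("with all statistical tests being two-sided and significance set at 0.05") and the model for the treatment effect ("The generalized estimating equation (GEE) model, which could test the effects of group, time, and their interactions, will be used"). Outcomes are taken at three visits (T0, T1, T2), so the group-by-time interaction has 2 degrees of freedom. Under Missing data management, missing values are not imputed for the GEE, so it uses the available visits.

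The number of independent units is set under Sample size and sampling. The evaluable number is given as "each study group will have 18 individuals to identify a standardized effect size of 0.40"; the stated power is 80% at the two-sided 5% level. With an allowance of 20% for attrition, the article then says that "23 participants per group (i.e., 46 participants in total) will be recruited". The same section appeals to the central limit theorem to say that 30 to 40 participants suffice for means, standard deviations and 95% confidence intervals.

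The article does not state the covariance estimator (robust or model-based), the working correlation, the reference distribution or any small-sample correction.

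**The concern.** The robust variance in GEE is built from the residuals of the independent units. With few units it is biased downward, because fitted residuals are smaller than true errors. The usual Wald chi-square (or z) reference also ignores that the variance has been estimated. Both errors act in the same direction: standard errors are too small, intervals too narrow and p-values too low.

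With 18 to 23 participants per arm the stated 5% level would then not be the level delivered, for either primary outcome (NUCOG total and BDI-II). The article considers small samples elsewhere: it gives small-sample validity as a reason for multiple imputation and for Cohen's d. For the GEE, the merits it gives are that it tests the interaction and accommodates missing data. The central limit theorem statement may suggest to a reader that this sample size is enough for the intervals, which the uncorrected sandwich variance does not bear out.

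**Working it through.** **Inputs.** From the article: 18 per arm evaluable, 23 per arm randomised, three visits, two-sided 0.05, GEE with group, time and their interaction. Assumed, because not stated: uncorrected robust variance with a chi-square or z reference. The 18 per arm is taken as given; whether it follows from the effect size of 0.40 is a separate question.

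**Reproducing the plan's figure.** 18 / (1 − 0.20) = 22.5, rounded up to 23 per arm, 46 in total. This agrees with the article.

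**Set-up for complete data.** With a full group-by-time mean and no covariates, the GEE estimates are the cell means, and the sandwich variance is the sample variance with denominator n in place of n − 1. For normal data with equal arms of size n, let ν = 2n − 2.

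**Single contrast (for example group by T1).** The Wald statistic equals t² × n/(n − 1), with t on ν df. The test therefore rejects when |t| > 1.96 × √((n − 1)/n).
- n = 18: threshold 1.905 on 34 df, true level 6.5%.
- n = 23: threshold 1.917 on 44 df, true level 6.2%.

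Coverage of a nominal 95% interval is therefore 100 − 6.5 = 93.5% and 100 − 6.2 = 93.8%. Relative to the correct t interval, the width is √(17/18) × 1.960/2.032 = 0.937 at 18 per arm (about 6% too narrow) and √(22/23) × 1.960/2.015 = 0.951 at 23 per arm (about 5% too narrow).

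**Joint 2-df group-by-time test.** The Wald statistic is Hotelling's T² × n/(n − 1), compared with 5.991. It rejects when T² > 5.991 × (n − 1)/n. For two dimensions the tail probability is (1 + T²/ν)^(−(ν − 1)/2).
- n = 18: T² threshold 5.659; (1 + 5.659/34)^(−16.5) = 7.9%.
- n = 23: T² threshold 5.731; (1 + 5.731/44)^(−21.5) = 7.2%.

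Simulation of 200,000 null trials per setting gave the same values (7.9% and 7.2%) at within-person correlations of 0.3, 0.5 and 0.8, so with complete data the result does not depend on the correlation.

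**Dropout, covariates and skewness.** Full GEE fits, 6,000 null trials per setting, true correlation 0.5, Monte Carlo standard error about 0.33 points. Covariate and skewed-outcome rows use an exchangeable working correlation.

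| Setting | 2-df test | T1 contrast |
|---|---|---|
| 23 per arm, 20% random dropout | 7.1% | 6.2% |
| same, 3 covariates | 7.5% | 6.3% |
| same, skewed outcome | 7.1% | 6.1% |
| 18 per arm complete, 3 covariates | 7.1% | 6.0% |
| 18 per arm complete, skewed outcome | 7.0% | 6.0% |

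Other runs at correlation 0.6, with 23 per arm and 20% random dropout, gave 7.3 to 7.6% (12,000 trials per dropout pattern) and, in one set of 8,000 trials, 8.0% for the 2-df test.

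**After correction.** With the n − 1 variance and a t or F reference, the simulated level is 4.9 to 5.1% for both tests. With a Mancl-DeRouen sandwich and a t/F reference on n − 2 df (n being the number of participants), it is 4.4 to 5.0%.

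**The case against.** The strongest objection is that the article never says a robust Wald test will be used. That setting is an assumption, and the choice of variance estimator is a detail an article may leave to a full protocol or analysis plan that is not shown. A reader might infer that the plan commits to an uncorrected test, or that silence about a correction is itself an error; the text supports neither. In the simulations, model-based standard errors with an exchangeable working correlation kept the joint test at 4.9 to 5.6%.

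This stands, and it makes the finding conditional. It does not remove it. The article does fix a method with large-sample inference and a sample of this size. Model-based errors are also a safe alternative only if the working correlation is right: it was right by construction in those runs. With an independence working correlation and true correlation 0.5, the model-based joint test rejected in only 0.3 to 0.5% of null trials.

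A second objection concerns size. About 8% is the top of the range for the joint test, and a single contrast exceeds 5% by only about 1.2 to 1.5 points. Cohen's d, which the article also reports, is a point estimate and is unaffected. This stands too.

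Third, a reader might infer that the inflated test would wrongly send the intervention to a full-scale trial. The documents do not support this. No progression rule depends on a GEE p-value; feasibility and acceptability are defined by recruitment, retention, dropout, adverse events, satisfaction and adherence. The Discussion says the pilot can show only preliminary effectiveness and will inform the design of a later trial.

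**Conclusion.** The concern holds in conditional form and is modest. If the GEE is run with the ordinary uncorrected robust Wald test, the group-by-time test at nominal 5% has a true level of about 7 to 8%. A single time-point contrast has about 6.2 to 6.5% (exact, complete data), with interval coverage of about 93.5 to 93.8%.

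These figures assume independent participants, a null effect and, where there is dropout, that it is random. The exact values also assume normal data and equal arms without covariates; the simulated cases with covariates or skewed outcomes were similar. The figures do not show that the article has chosen this variance estimator. The consequence is intervals for both primary outcomes that are about 5 to 6% too narrow, in a pilot whose effect estimates are meant to inform a later trial.

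**What to change.** State a small-sample method for the continuous outcomes, in one of two ways:

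1. Replace GEE with a linear mixed model for repeated measures, fitted by REML, with group, time and their interaction and Satterthwaite (or Kenward-Roger) degrees of freedom. It uses all available visits without imputation, so it keeps the missing-data advantage the article cites for GEE, and a mixed-model procedure is in the SPSS package already named.
2. Keep GEE, but specify a bias-corrected sandwich variance (for example Mancl-DeRouen) with a t or F reference. Check first that the named software offers it.

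In either case, name the group-by-time contrast at T1 with its 95% confidence interval as the effect reported for each primary outcome. If a fuller analysis plan already specifies such a method, a sentence in the protocol saying so is enough.

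The cost is a change of wording, with no new data or participants. The downside is slightly wider intervals and slightly larger p-values.

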### Randomization and blinding

2.3

Randomization will be performed through the minimization method (28) to balance the pertinent influencing factors for cognitive function and the intervention effectiveness (i.e., motor imagery ability (29), age, and educational level). Minimization entails assigning intervention to succeeding trial participants based on the characteristics of previously enrolled participants (excluding the first participant who receives a random allocation) to enhance balance among the groups in key variables of interest. An independent administrative clerk will conduct this procedure by using the Minim software and will subsequently provide the researcher with a sequentially numbered, sealed, opaque envelope containing the group assignment for the participants. Due to the nature of the intervention, participants and the researchers who will enroll in the intervention process and qualitative interviews will not be blinded. However, the baseline and outcome assessor, as well as the data analyst, will remain blinded to group assignment.

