To analyze fMRI data, differences of each group at baseline and post-intervention will be evaluated using the paired *t-test* in Statistical nonParametric Mapping (SnPM); differences between groups (intervention group vs. control group) will be assessed using a two-sample *t-test*. Differences between the two groups of the study over time will be evaluated using a General linear model, in which group and time will be included as distinct factors (2 × 2 factorial design). Multiple linear regression models will be used, with age, education level, and motor imagery ability as covariates, to assess the correlation between changes in MRI results and changes in cognitive function and depression data after intervention (69). For DTI data, statistical analyses will be performed using non-parametric permutation testing with 5,000 Monte Carlo simulations. We will look for differences in fractional anisotropy between the groups, accounting for age, educational level, and motor imagery ability as regressors of no interest in the general linear model. A two-sample *t* test will be used to evaluate the between-group differences in DTI metrices (e.g., path length, clustering coefficient, global efficiency, local efficiency, strength, and small world attribute). Association analysis between altered white matter microstructure imaging data and the assessments of cognitive function and depression will be analyzed with Spearman’s correlation coefficient (70).

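### Covariates for the clinical outcomes are chosen by baseline significance tests, a rule that minimisation all but prevents from selecting the protocol's own prognostic factors

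*Protocol article*

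**What the plan says.** Section 2.3 (Randomization and blinding) allocates by minimisation in order to "balance the pertinent influencing factors for cognitive function and the intervention effectiveness", and names these factors as "motor imagery ability (29), age, and educational level".

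Section 2.7.1 (Quantitative data analyses) compares the groups by t-test or Mann-Whitney test, and by chi-square or Fisher test, at all three visits: "As for group differences at baseline, post-intervention, and follow-up". It works throughout "with all statistical tests being two-sided and significance set at 0.05". The model for the clinical outcomes is a GEE, "which could test the effects of group, time, and their interactions, will be used to analyze the effects of the intervention". The only covariate rule for that analysis is: "Covariance (if any found in the baseline comparison) will be adjusted during the analysis of intervention effects". On its natural reading, covariance here means covariates, and a variable is found when its baseline test is significant. No section fixes a covariate for cognition, depression or the other clinical outcomes.

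Section 2.7.3 (MRI data analysis) is different in two places. The regression of MRI change on clinical change takes age, education and motor imagery ability as covariates, and the fractional anisotropy model is fitted "accounting for age, educational level, and motor imagery ability as regressors of no interest". No covariates are stated for the other MRI comparisons.

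**The concern.** The allocation method and the covariate rule work against each other. Minimisation suppresses between-group differences in three variables because they are believed to drive outcome. The rule then admits a covariate only when such a difference appears. The strongest expected predictors are thus left out of the primary-outcome analysis, while variables imbalanced by chance, prognostic or not, may enter.

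Three things are at stake. The form of the primary model depends on the data. Comparisons that ignore balanced prognostic factors carry standard errors that are too large for the design. And a trial of 46 people gives up precision that its own baseline data could supply, although section 2.6 says the trial is to estimate the between-group effect and the Discussion says it will inform a full-scale trial.

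**Working it through.** **Sample size used.** Section 2.6 gives 18 per group and 20% attrition: 18 / (1 - 0.20) = 22.5, rounded up to 23 per group, 46 in total. This reproduces. The checks use N = 46 and N = 36 (18 per group). The plan gives no figure for the covariate rule itself.

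**Simulation assumptions (none is in the protocol).** Three-factor minimisation with three levels per factor; probability 0.8 or 1.0 of assignment to the better-balancing arm; factors explaining 20% or 40% of outcome variance; baseline-outcome correlation rho of 0.5 or 0.7; linear models at one post-baseline visit rather than the full GEE; 2,500 runs per setting. The Monte Carlo standard error near 5% is sqrt(0.05 x 0.95 / 2500) = 0.4 percentage points.

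**1. How often would the rule select a minimisation factor?** The chance that at least one of the three reaches p < 0.05 at baseline is 0-1.0% under minimisation, against 14.6% under simple equal allocation. A baseline outcome score is flagged in 1.9-4.3% of trials.

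**2. What would it select instead?** Section 2.5.1 lists 14 characteristics (smoking and alcohol counted separately). Section 2.5.3 gives about 10 baseline scores: NUCOG, BDI-II, digit span forward and backward, SDMT, Stroop, pain severity, pain interference, exercise self-efficacy and KVIQ-10. Removing age, education and KVIQ-10 leaves 24 - 3 = 21.
- P(at least one p < 0.05) = 1 - 0.95^21 = 0.659.
- Expected number flagged = 21 x 0.05 = 1.05.

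The 66% is close to an upper bound. It assumes that all 21 are tested, independently and at exactly 5%. The cognitive scores should correlate, and Fisher tests at this size run below 5%.

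**3. Type I error (nominal 5%).**
- Unadjusted post-intervention comparison: 1.7-3.9%.
- Covariates chosen by baseline test: 1.8-3.7%, so the rule does not repair it.
- Three factors fixed: 4.4-5.8%.
- Three factors plus baseline score fixed: 4.3-5.8%.
- Change score, the analogue of group-by-time with T0 as a response: 4.3-5.4% with no covariates, because factor effects that are constant over time cancel.

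The mechanism shows in the d = 0.4 run below: the unadjusted comparison reports a standard error of 0.294, while its estimates actually vary with a standard error of 0.262.

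**4. Precision of group-by-time.** With equal variances, a change score has variance proportional to 2(1 - rho) and a baseline-adjusted comparison to 1 - rho^2. The ratio is (1 - rho^2) / [2(1 - rho)] = (1 + rho)/2.
- rho = 0.5: 0.75, so 25% lower variance.
- rho = 0.7: 0.85, so 15% lower variance.

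**5. Power** at N = 46, factors explaining 30% of variance, rho = 0.6:
- d = 0.4: unadjusted 0.24; test-selected covariates 0.24; change score 0.31; three factors fixed 0.34; factors plus baseline 0.40.
- d = 0.8: 0.77; 0.78; 0.84; 0.88; 0.93, in the same order.

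The step from 0.31 to 0.40 reflects moving baseline to the covariate side and adding the three factors together.

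**The case against.** The strongest reply is that the planned analysis of intervention effects is the GEE with group, time and their interaction. If T0 is one of its responses, as the three-visit design suggests, group-by-time compares change from baseline and keeps its nominal error without any covariate. This stands. A reader might infer that omitting the minimisation factors invalidates the main test, or that baseline scores count only when imbalanced by chance. The documents do not support either on that reading: the interaction uses the baseline score in every case. The second inference would hold only if the GEE took T1 and T2 alone as responses, and section 2.7.1 does not say which. If T0 is a response and its score is also flagged at baseline, the rule would use that score twice.

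A reader might also infer that the MRI analyses as a whole adjust for the three factors. They do so only in the change regression and the fractional anisotropy model. The fMRI t-tests, the two-by-two group-by-time model, the t-tests on DTI metrics and the Spearman correlations state no covariates. The inconsistency with the clinical analysis is therefore partial.

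It is also fair that a chance covariate does not in itself bias a randomised comparison, that baseline as response or as covariate is a choice between two valid methods, and that this is a pilot. None of this defends selection by baseline test.

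Finally, the remedy has a cost of its own. In a further simulation (6,000 runs, three-factor minimisation, complete data, independence working correlation, rho = 0.6, factors explaining 30% of variance), the proposed model fitted as an uncorrected GEE with robust standard errors had type I error of 6.9% at N = 46 and 7.6% at N = 36. The planned group-by-time contrast had 6.0% and 5.7%. This stands too, so the fix needs a small-sample correction.

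**Conclusion.** The point holds for the clinical outcomes. The covariate rule is a stated choice rather than something left to a fuller document, and it conflicts with the allocation design: the three factors would be selected in about 0-1% of trials, while up to about 66% of trials would adjust for at least one chance imbalance.

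The consequences differ by analysis. The separate T1 and T2 tests and any group main effect are conservative, at about 1.7-3.9% instead of 5%. The group-by-time test with T0 as a response remains valid; its cost is precision, with a variance 15-25% lower available from using baseline as a covariate and simulated power of 0.31 against 0.40 at d = 0.4.

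These sizes rest on assumed variance explained, correlation, factor levels and assignment probability, and on linear models at a single visit. The direction was the same across the ranges tried. The change should be made, but the flaw does not invalidate the trial.

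**What to change.** Delete the baseline-test rule in section 2.7.1. For each clinical outcome, prespecify one model with:
- T1 and T2 as responses, and group, time and group-by-time as effects;
- the baseline value of that outcome as a covariate, and not also as a response;
- age, educational level and KVIQ-10 as covariates whatever the baseline comparison shows;
- a small-sample correction to the GEE standard errors, or an equivalent mixed model.

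Report the adjusted group difference at T1 and at T2 with 95% confidence intervals. Keep the baseline table and the unadjusted T1 and T2 comparisons descriptive. Adding the three factors only as main effects to a model with T0 as a response would not be enough, because the group-by-time contrast would not change.

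The cost is a few sentences of analysis wording and about four degrees of freedom (baseline value, age, education, KVIQ-10), more if education is categorical. All variables are already collected at T0, and the data analyst is to remain blinded, so the change can be fixed before allocation is revealed.

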### Outcome measures

2.5

A trained research assistant, blinded to group allocation, will conduct a series of assessments at three time points: baseline (T0), after the 8-week intervention program (T1), and 1 month post-intervention (T2). Socio-demographic variables, feasibility and acceptability indexes, and effect outcomes are included. The effect outcomes include primary outcomes (global cognitive function and depression) and secondary outcomes (neurocognitive domains, multimodal MRI findings, chronic pain, self-efficacy for exercise, and motor imagery ability). The assessments will be conducted during participants’ visits to the study site (University campus) (Table 1).

**Table 1 tab1:** Data collection schedule.

Assessment items	Study period			
	Enrollment	Allocation	Post-allocation	
	−T1	T0 Baseline	T1 Post-intervention	T2 1-month follow-up
Enrollment				
Eligibility screening	X			
Informed consent	X			
Allocation		X		
Assessments				
Socio-demographics and medical history		X		
Feasibility of the intervention		X		X
Acceptability of the intervention			X	
Intervention effectiveness				
Primary outcomes				
Global cognitive function		X	X	X
Depression		X	X	X
Secondary outcomes				
Cognitive domain-attention		X	X	X
Cognitive domain-executive function		X	X	X
Multimodal MRI findings		X	X	
Chronic pain		X	X	X
Self-efficacy for exercise		X	X	X
Motor imagery ability		X	X	X

MRI, magnetic resonance imaging.

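### Cohen's d is defined without a baseline term or a visit; adjusting it for the T0 score would make it more precise and more consistent with the model results

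*Protocol article*

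**What the plan says.** Section 2.7.1 (Quantitative data analyses) assigns the intervention effect to a GEE model, "which could test the effects of group, time, and their interactions, will be used to analyze the effects of the intervention". Baseline covariates enter only conditionally: "if any found in the baseline comparison) will be adjusted during the analysis of intervention effects". The same section plans unadjusted two-group tests at each visit, introduced by "As for group differences at baseline, post-intervention, and follow-up".

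Cohen's d "will be used as the unit measure of effect size", with cut-offs of 0.2, 0.5 and 0.8 for small, moderate and large. Its formula is "difference in treatment and control group means divided by the pooled standard deviation". No visit is named, and no baseline, change-score or model-based term appears.

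Section 2.6 (Sample size and sampling) says the sample is meant "to evaluate intervention feasibility and estimate the between-group effect". Section 2.5 and Table 1 show both primary outcomes, NUCOG and BDI-II, measured at T0, T1 and T2. The minimization factors in section 2.3 are "motor imagery ability (29), age, and educational level"; the baseline scores of the two primary outcomes are not among them.

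**The concern.** In a trial of this size the arms can differ noticeably at T0 by chance. A d built from post-intervention means passes part of that difference on to the reported effect size, although the T0 scores needed to remove it are collected in everyone. The promise to adjust for baseline differences is made for the analysis of intervention effects and does not clearly reach d, which has its own formula.

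Estimating the between-group effect is a stated purpose of the pilot, and the Discussion says the results will help to design a full-scale trial. At stake are a noisier estimate than necessary and a paper in which d and the GEE result may look different in size without explanation.

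**Working it through.** **Inputs from the protocol.** 18 analysable per arm and a standardized effect of 0.40 (section 2.6). Allowing for 20% attrition, 18 / 0.80 = 22.5, which rounds up to the stated 23 per arm. The 18 is taken as given here; whether it follows from an effect of 0.40 is a separate question. The protocol gives no figure for the precision of d, so there is none to reproduce.

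**Assumptions.** The correlation r between the T0 and T1 scores is not given; 0.5, 0.7 and 0.8 are used. Outcomes are normal with equal SDs at each visit, and randomization is simple.

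**Step 1: chance difference at T0.** Its SD in outcome-SD units is sqrt(2/n).
- n = 18: sqrt(2/18) = 0.33, 95% range ±0.65. It exceeds 0.40 in absolute value in 23% of trials.
- n = 23: sqrt(2/23) = 0.295, 95% range ±0.58. It exceeds 0.40 in 17% of trials.

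**Step 2: how much enters d.** Given a T0 difference b, the expected shift in the post-score difference is r × b. For b = 0.33 this is 0.17, 0.23 and 0.27 at r = 0.5, 0.7 and 0.8. Against the planned 0.40, that is roughly 40% to 65%.

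**Step 3: precision, treating the outcome SD as known.** The unadjusted difference has SD sqrt(2/n). With the T0 score as covariate it is sqrt(2/n) × sqrt(1 − r²).

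| n per arm | Unadjusted | r = 0.5 | r = 0.7 | r = 0.8 |
|---|---|---|---|---|
| 18 | 0.33 | 0.29 | 0.24 | 0.20 |
| 23 | 0.295 | 0.26 | 0.21 | 0.18 |

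**Step 4: the same for d itself.** Simulated trials with 18 per arm, a true d of 0.40, and the SD and covariate slope estimated in each trial give an SD of about 0.35 for the unadjusted d. The adjusted d has 0.31, 0.25 and 0.22. These are slightly larger than in step 3 because the divisor and slope are also estimated. Both versions average about 0.41, so neither is favoured on bias.

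**Step 5: distance between the two versions of d.** With a common divisor they differ by r × b, which has SD r × 0.33. A gap above 0.2 therefore occurs with probability 2 × [1 − Φ(0.2 / (r × 0.333))], which is 23%, 39% and 45% at r = 0.5, 0.7 and 0.8. If the adjusted d is divided by the baseline SD, simulation gives 28%, 41% and 47%.

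**Step 6: is the plain group-by-time contrast a good substitute?** The difference in mean change has SD sqrt(2/n) × sqrt(2(1 − r)). At n = 18 and r = 0.5 this is 0.33 × 1 = 0.33, the same as the unadjusted post-score difference; at r = 0.3 it is 0.39, which is worse. Its correlation with the T0 difference is −0.5 at r = 0.5, so it carries the chance imbalance in the opposite direction. It gains precision only when r exceeds 0.5, and the covariate-adjusted estimate has the lower SD at every value of r examined.

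**The case against.** The formula is the textbook definition of Cohen's d. The text does not say that the means are raw, does not name a visit, and does not say that d is calculated outside the model; model-estimated means or mean changes could be meant. This is fair as far as it goes. Even so, the plain reading is observed means, which fits the unadjusted tests at each visit in the same section. An analyst following the formula as written would calculate that.

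A reader might go further and infer that d is meant to express the group-by-time estimate and so contradicts it. The documents do not support this. They never tie d to the interaction, and a d from visit means is a natural companion to the per-visit tests. In simulation with a true d of 0.40, d and the difference in change have opposite signs in about 13% to 15% of trials at 18 per arm. Both are noisy estimates, so that figure counts disagreements, not errors in d.

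A post-score d is also unbiased under randomization and widely reported. That stands, and it limits the point to precision and consistency. Minimizing on age, education and motor imagery ability, chosen partly as influences on cognition, should also shrink chance imbalance in NUCOG below the simple-randomization figures. That stands too; the documents do not allow its size to be calculated. Finally, the GEE will still give estimates on the original scales, so d is the only standardized measure named but not the only effect estimate available.

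**Conclusion.** The point holds as a recommendation. As written, d is most naturally an unadjusted post-score measure with no visit attached. It leaves unused a T0 score that is already collected and that would narrow its SD from about 0.35 to between 0.31 and 0.22 at 18 per arm. The gain is modest at a correlation of 0.5 and substantial at 0.7 or above. These figures rest on an assumed correlation, equal SDs at each visit and simple randomization, and they may overstate the imbalance for NUCOG.

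It would be wrong to conclude that d is biased, that the plan computes an invalid effect size, or that it must conflict with the GEE. The two can differ when reported side by side, and the reader would then have no stated way to reconcile them.

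**What to change.** Replace the formula with a definition of d at T1, and separately at T2, as the between-group difference adjusted for the T0 score of the same outcome (T0 score as covariate), divided by the pooled baseline SD, with a 95% CI. Do not use the unadjusted group-by-time contrast as the numerator, for the reason in step 6. The unadjusted post-score d can stay as a descriptive figure.

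The cost is one sentence in section 2.7.1 and minor programming; no new data are needed. The drawback is that the adjusted d is less directly comparable with studies that report a post-score d, which is the reason to keep the descriptive version.
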